# Multicentre randomised controlled trial of a group psychological intervention for postnatal depression in British mothers of South Asian origin (ROSHNI-2): study protocol

**DOI:** 10.1192/bjo.2021.1032

**Published:** 2021-12-01

**Keywords:** Perinatal psychiatry, depressive disorders, cognitive–behavioural therapies, psychosocial interventions, randomised controlled trial

## Abstract

**Background:**

In the UK, postnatal depression is more common in British South Asian women than White Caucasion women. Cognitive–behavioural therapy (CBT) is recommended as a first-line treatment, but there is little evidence for the adaptation of CBT for postnatal depression to ensure its applicability to different ethnic groups.

**Aims:**

To evaluate the clinical and cost-effectiveness of a CBT-based positive health programme group intervention in British South Asian women with postnatal depression.

**Method:**

We have designed a multicentre, two-arm, partially nested, randomised controlled trial with 4- and 12-month follow-up, comparing a 12-session group CBT-based intervention (positive health programme) plus treatment as usual with treatment as usual alone, for British South Asian women with postnatal depression. Participants will be recruited from primary care and appropriate community venues in areas of high South Asian density across the UK. It has been estimated that randomising 720 participants (360 into each group) will be sufficient to detect a clinically important difference between a 55% recovery rate in the intervention group and a 40% recovery rate in the treatment-as-usual group. An economic analysis will estimate the cost-effectiveness of the positive health programme. A qualitative process evaluation will explore barriers and enablers to study participation and examine the acceptability and impact of the programme from the perspective of British South Asian women and other key stakeholders.

Postnatal depression is a major public health concern because of its negative effect on mothers, including relationship problems^1,2^ and an increased risk of future depression. In the UK, postnatal depression is more common in British South Asian women than White women.^1,3^ Postnatal depression also negatively influences the psychological and cognitive development of children.^2^ Postnatal depression is treatable,^4,5^ but women can be reluctant to disclose symptoms and seek help because of stigma.^6,7^ Antidepressants can be an effective treatment, but new mothers can be reluctant to use them because of concerns about side-effects.^4,5^ Cognitive–behavioural therapy (CBT) has been shown to be effective for postnatal depression^4,5^ and is endorsed as a first-line treatment.^8^ However, there is little empirical evidence for the adaptation of evidence-based treatments, including CBT, to ensure their applicability to different ethnic groups.^9,10^ There is value in cultural adaptation and a need to test the effectiveness of adapted interventions for ethnic minority groups.^11^

## The need for culturally adapted CBT

The positive health programme (PHP) is a culturally adapted group CBT intervention for postnatal depression^10^ that has been developed by our research group in an exploratory randomised controlled trial (RCT) (Exploratory RCT of a Group Psychological Intervention for Postnatal Depression in British Mothers of South Asian Origin; ROSHNI-D),^12^ and we were able to show the feasibility and acceptability of the present trial. A sufficiently powered trial is needed to confirm the preliminary findings of ROSHNI-D, to test both short- and longer-term outcomes, and to answer additional research questions, including the cost-effectiveness of PHP. The focus of the proposed study is a group CBT intervention for British South Asian women with postnatal depression and psychosocial difficulties. These women often live in low-income areas and, because of their psychosocial problems, language and cultural barriers, they are deemed ‘hard to reach’ and hard to engage. South Asian people comprise the largest ethnic minority group in the UK, representing around 7.5% (4 214 000) of the population,^13^ and have one of the highest birth rates in the UK. There are now policies that endorse the need for a range of effective therapies, including psychotherapeutic treatments, that are culturally appropriate and effective.^14^

## Aims and hypothesis

The present trial, ROSHNI-2, aims to evaluate the clinical and cost-effectiveness of the PHP intervention added to treatment as usual (TAU), compared with TAU only, in British South Asian women with postnatal depression. *Roshni* means light in Urdu/Hindi. The primary hypothesis is that participants who receive PHP added to TAU will have reduced levels of postnatal depression, as measured by the Hamilton Rating Scale for Depression (HRSD),^15^ compared with participants receiving TAU only, 4 months after randomisation (end of intervention). HRSD scores at 4-month follow-up will be the primary outcome measure. Costs associated with health and social care resource use will be collected, and each participant in the trial will be asked to complete the EuroQol EQ-5D instrument at each follow-up, and these responses will be converted to quality-adjusted life years (QALYs). Follow-up at 12 months will provide evidence of long-term outcomes. A qualitative process evaluation will explore barriers and enablers to study participation, and examine the acceptability of PHP from the perspective of British South Asian women, the impact of PHP on healthcare practice from the perspectives of general practitioners (GPs), and the experiences of being trained in and delivering PHP from the perspectives of group facilitators.

## Method

### Design

This is a multicentre, two-arm, rater-blinded, partially nested RCT with post-intervention (4 months) and 12-month follow-up, comparing PHP and TAU with TAU only, for British South Asian women with postnatal depression. There is a likelihood that because of the reciprocity between participants during the group PHP intervention, they will respond in a similar manner and their outcomes will be more alike than for women in different groups. This leads to a clustering effect in the intervention condition similar to that found in cluster randomised trials. The trial design adopts a partially nested design with participants in the intervention arm nested in therapy groups compared with the control arm participants, who are not nested. Economic and process evaluations are also embedded in the trial. The trial is registered with Clinicaltrials.gov under registration number ISRCTN10697380.

### Internal pilot phase

An internal pilot phase is integrated into the trial, with clear STOP/GO criteria to prove viability to proceed to a full trial across all study sites. Success criteria during the internal pilot study phase (months 5–14) will be gauged by recruitment of at least 200 participants. In case this is not possible and we face difficulties in achieving the target, we will look into the possible shortcomings and have a ‘rescue plan’ ready for deliberation by the Trial Steering Committee and National Institute for Health Research approval.

STOP/GO criteria are as follows: GO if ≥180 participants are recruited into the study (target minus 10%), implement rescue plan if ≥120 (60%) but <180 (90%) participants are recruited into the study, and STOP if <120 (60%) participants are recruited into the study.

### Setting

Participants are recruited from general practices, children's centres and other appropriate community venues in areas with a high South Asian population across different locations in the UK (North-West, Yorkshire, Midlands, London and Glasgow). Local principal investigators lead the conduct of the trial in each location, and are supported by the ROSHNI research team, all of whom, including principal investigators, are trained in good clinical practice.

### Study population

Participants are women of self-ascribed British South Asian origin who live with their infant(s) aged ≤12 months, have postnatal depression and will reside in the geographical area of the study for the duration of their participation.

#### Inclusion criteria

The inclusion criteria are as follows: self-ascribed British South Asian women as mentioned by the Office of National Statistics,^13^ aged 16 years or older; living with their infant(s), who are aged up to 12 months; and meet the DSM-5 criteria for depression as confirmed by the Structured Clinical Interview for the DSM (SCID).^16^

#### Exclusion criteria

The exclusion criteria are as follows: diagnosed physical or intellectual disability that prevents participation in the trial, postpartum or other psychosis, or active suicidal ideation.

The exclusion criteria will not include ongoing use of antidepressant medication and earlier self-reported common mental illness, including prior postnatal depression. Medication use will be recorded in the baseline and follow-up assessments, and this information will be considered at analysis.

### Recruitment

Potential participants will be approached via GPs, children's centres, baby clinics, community centres, pharmacies and other relevant locations. The study is promoted in each of these locations, using materials that have been produced as a joint collaboration with the patient group, and appear in English, Urdu, Hindi, Bengali, Gujarati and Tamil. Community contact has already been initiated through partnerships with voluntary sector organisations, and the research team has started regular liaison meetings with the local health visitors, GPs and children's centres, for study promotion. Specific inputs are also being taken from the community organisations related to trial design, recruitment methods and the intervention content.

Participating GPs send a letter to all 6-week postnatal British South Asian women informing them about the trial and inviting them to take part. The letter includes the Patient Health Questionnaire 9 (PHQ-9),^17^ a participant information sheet (PIS) and a response slip. Potential participants are asked to complete the PHQ-9 and consent-to-contact form, and return these to their local study site via pre-paid envelope. Postal and telephone reminders are sent to those who do not respond. In addition, GP records are monitored for non-responders so that primary care staff can remind women about the study at routine appointments. When the PHQ-9 and consent-to-contact forms are completed and returned, the research assistants will then make contact and arrange to speak to the participant in a convenient location, to provide further detail on the study and take consent.

Potential participants are also identified by the research team via GP case records. With the GP's permission, identified mothers are contacted either directly by phone or in person, by a clinical support officer, research nurse or GP administration staff, with the support of a bilingual member of the research team. To further ensure efficient recruitment, the research team visits local children's centres, baby clinics and other relevant locations, where potential participants are invited to take part and are provided with a PIS. Women who fulfil trial eligibility criteria are invited to provide written informed consent for trial participation and baseline assessment. All participants will be given ample opportunity for clarifications and time to consider before signing the consent form. The research team will advise participants that their participation in, or departure from, the trial does not affect any aspect of their usual care. Once a patient has agreed to participate and signed a consent form, they are then asked to complete the PHQ-9. Participants who score ≥10 are eligible to progress to the second stage of assessment of eligibility. Mothers who score <10 on the PHQ-9 at first screen will be again invited for a further assessment after 12–16 weeks to complete the PHQ-9 again, if within the 52-week postnatal period, to ascertain that later-onset postnatal depression is not missed.

The second stage of recruitment/assessment of eligibility is an interview with the SCID.^16^ This is administered by trained members of the research team at baseline to confirm the diagnosis of depression. The SCID is a semi-structured interview that consists of standardised diagnostic questions arranged in modules corresponding to each DSM-5 Axis.^16^ The SCID has been used in a large RCT of psychological intervention for postnatal depression with a multicultural population in Canada.^18^ The PHQ-9 has been translated and validated in Urdu.^19^ In cases where the SCID confirms depression, women are asked to confirm consent to take part in the study. In cases where the SCID does not confirm depression, these women are not randomised.

Our previous experience of research with British South Asian mothers who have postnatal depression indicates that engagement with participants’ families is fundamental to success, and that this should begin at the time of screening. Therefore, at the potential participant's discretion, researchers will share details of the study with other family members. Contact details will also be provided for a bilingual senior investigator who will be available to converse with the family if needed. The first study participant was recruited on 8 February 2017.

### Randomisation

Participants are randomised via an independent remote telephone randomisation service based at the Manchester Clinical Trials Unit. PHP is based on groups of between five and nine participants, and randomisation is stratified by centre and will use a block size of 10–18, depending on the size of the site, so that five to nine participants are allocated to PHP plus TAU and five to nine participants are allocated to TAU only. All efforts are made to ensure that the time period between baseline assessment and randomisation will be no longer than 4–6 weeks. The GP is informed about their patient's participation in the trial and treatment allocation by a letter, to be kept with the participant's medical notes.

It is not possible to blind participating mothers, their GPs or practice health visitors to treatment group. Researchers who are blind to treatment allocation will collect the outcome measures. To minimise selection bias and maximise external validity, we will recruit mothers across geographies in the UK and aim to keep the exclusion criteria to a minimum.

### Intervention

PHP is a manual-assisted, culturally adapted, group psychological intervention delivered by two trained, bilingual facilitators (one lead facilitator and a co-facilitator). PHP is based on the principles of CBT, and has been found to be acceptable by participants in previous studies of postnatal depression in British South Asian women.^10^ In ROSHNI-2, 12 group PHP sessions are delivered in total; sessions are delivered once a week for the first 2 months, and then fortnightly for the following 2 months. Each group session lasts 60–90 min, and at the start of each session participants are reminded about confidentiality and are assured by facilitators that any disclosures they make will remain confidential, with the exception of any intentions of harming oneself or others. The sessions covered within the PHP include identifying the pressures and expectations of being a South Asian woman, understanding and managing self-esteem, ‘keeping up with the Chaudhry's’, exercise and looking good, religion and spirituality, relaxation and ‘taking time out’, assertiveness and confidence building, breaking social isolation and building social networks, and practising CBT techniques and assessing change and developing relapse prevention plans.

The processes through which PHP was culturally adapted are described in detail elsewhere.^10,12^ The PHP manual is available in English, Urdu, Hindi, Bengali, Gujarati and Tamil. Before each group starts, facilitators are matched to groups according to languages most commonly spoken by group participants. All facilitators are fluent in English and one or more of the study languages. Our earlier findings point out that when working with diverse populations, the venues where the intervention is delivered should be kept as neutral as possible and ‘not owned’ by a specific ethnic or religious group.^10^ Therefore, PHP is delivered at children's centres and other community venues, as these are considered more acceptable to the British South Asian community than going for ‘therapy’ or ‘treatment’ in a medical setting. Transportation, child care and refreshments are provided to facilitate mothers’ attendance at group sessions. Health Research Authority guidance states that payment to participants in therapeutic research, in addition to reimbursement, are permissible, as they may reduce potential power imbalances by making participation seem less like a favour to a healthcare professional or researcher.^20^ Furthermore, in the UK it is standard practice to pay healthy volunteers and patient volunteers, therefore not paying others who also contribute to research would be unfair, and the benefits that participants may receive from the intervention do not mean that they should be barred from receiving payment. Participants are reimbursed with a £10 ‘love2shop’ voucher for their time and their travel expenses are also reimbursed. The intervention group will continue to receive routine assessment and management by the primary care team. With the written informed consent of participants, a few groups sessions are recorded for quality checks.

### Training, supervision and competency assurance

PHP facilitators are of different backgrounds and have varying levels of experience of delivering psychological interventions in the British South Asian community. Each facilitator received two full days training, which is delivered by PHP trainers who are mental health professionals and therapists by background ([name], [name]). The content of each PHP session is covered during training, and time is also spent on non-therapeutic specific skills, including engaging with participants, controlling PHP groups, listening skills and safeguarding. Didactic and Socratic teaching methods are used in PHP training and these are facilitated with presentations, group discussions and role-play methods. At least one out of 12 sessions is observed by PHP trainers, following which constructive feedback is provided and any areas that need improvement are highlighted. Monthly supervision is conducted by the PHP supervisory team and is available between sessions if deemed necessary by PHP trainers or requested by group facilitators. Supervision is conducted over the phone or via Skype in most instances, to account for the geographical distribution of groups and facilitators.

### Treatment as usual

TAU includes participating GPs carrying out routine assessment and management and may involve ongoing monitoring, Improving Access to Psychological Therapies/other services referral and antidepressant prescription.

### Outcome measures

Outcome measure data is collected at two time points: the end of intervention at 4 months, and 12 months after randomisation. The SCID is not repeated at the 4-month follow-up as it is used only as a diagnostic measure in ROSHNI-2, to establish diagnosis of depression (Table 1 and Fig. 1).

**Fig. 1 fig01:**
[figure not shown]
Consolidated Standards of Reporting Trials study flow diagram.

**Table 1 tab01:** Schedule of assessments

Procedures	Visits (insert visit numbers as appropriate)			
	Screening	Baseline	4 months (end of intervention)	12 months
Informed consent	X			
Demographics		X		
Socioeconomic data		X		
Study assessments				
PHQ-9		X	X	X
HRSD		X	X	X
SCID		X		
GAD-7		X	X	X
EQ-5D		X	X	X
Parenting Sense of Competence scale		X	X	X
Social functioning		X	X	X
IAPT Healthy Minds Patient Experience Questionnaire			X	X
EPQ		X	X	X
Ages and stages questionnaires		X		X

PHQ-9, Patient Health Questionnaire 9; HRSD, Hamilton Rating Scale for Depression; SCID, Structured Clinical Interview for the DSM; GAD-7, Generalized Anxiety Disorder-7: IAPT, Improving Access to Psychological Therapies; EPQ, Economic Patient Questionnaire.

### Primary outcome measure

At the 4-month follow-up, the primary outcome measure is the HRSD,^15^ which is a valid and reliable measure of severity of depression. A score of ≤7 on the HRSD will indicate remission/recovery from depression.

### Secondary outcome measures

Secondary outcome measures are as follows:
Treatment response will also be measured with the HRSD; treatment response criteria is a reduction of ≥50% in the HRSD baseline score of the participants.PHQ-9^17^: valid and reliable self-report measure of severity of depression; Urdu and Bengali versions of the PHQ-9 have been validated.^21^Generalized Anxiety Disorder-7 (GAD-7)^22^: a valid and reliable self-report measure of severity of anxiety; an Urdu version of the GAD-7 has been validated.^23^Parenting Sense of Competence^24^: a valid and reliable self-report measure of parental competence;^25^ Parental competence is measured on two dimensions of satisfaction and efficacy; the questionnaire has 16 items (nine on satisfaction and seven on efficacy) and is scored according to a six-point Likert scale, ranging from ‘1, strongly disagree’ to ‘6, strongly agree’.Social functioning^12^: a self-report measure rating difficulty in completing ten items concerning daily function; the questionnaire is scored according to a five-point Likert scale, ranging from ‘0, no difficulty’ to ‘4, often can't do the task’.Improving Access to Psychological Therapies Patient Experience Questionnaire^26^: a valid and reliable self-report measure of an individual's experiences of the intervention they participated in.Ages and stages questionnaires^27^: a valid and reliable parent-completed measure of childhood development; this series of 11 questionnaires each include 30 closed questions on five domains of child development; mothers will finish the questionnaire both at baseline and 12-month follow-up.EQ-5D-3L:^28,29^ a health status measure, which has five dimensions (mobility, self-care, usual activity, pain/discomfort, anxiety/depression); participants can rate themselves as having no problems, some or moderate problems or extreme problems (for pain/discomfort and anxiety/depression domains), or unable to do an activity (self-care and usual activity domains or confined to bed (mobility domain).Economic Patient Questionnaire (EPQ): health service use will be captured using an EPQ; in addition to the National Health Service (NHS) and social care, cost to the participant for services will also be collected; if women in either arm of the trial are receiving any other treatment, this information will be captured here.

All measures are available in Urdu, Hindi, Bengali, Gujarati and Tamil.

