### Sample size

We will recruit 720 participants and randomise 360 into each arm. With 40 closed groups of nine and 360 controls, the trial will have 90% power to detect a clinically important difference between a 55% recovery rate in the intervention and a 40% recovery rate in the control, assuming an intraclass correlation (ICC) for group treatment of 0.05, a 75% follow-up and a 5% significance level. The sample size calculation and data analysis take into account clustering because of the partial nested design. Statistical methods for the partially nested design have been discussed in other publications.^30^ Peer-reviewed work by scholars evaluating psychological treatments for postnatal depression points out that for the effect to be considered clinically meaningful, there needs to be a 20% absolute decrease in the number of mothers with depression post-treatment, endorsing the need to develop and implement such treatments. On the recommendation of the funding panel, we will be powered to detect a difference of 15% in the primary outcome between the two randomised arms. Our exploratory trial suggests that a 75% follow-up rate can be achieved at 4 months. Assuming this follow-up rate and an initial group size of nine women per group, the mean group size will be 6.75 women.

There is not enough reliable data related to the magnitude of therapy group clustering when evaluating psychological treatments for postnatal depression. Barrowclough et al give 30 estimates of the ICC for a group therapy, ranging from 0 (95% CI 0–0.29) to a maximum of 0.257 (95% CI 0.02–0.67), with a mean of 0.044 and median of 0.^31^ From the width of the confidence intervals, there is appreciable uncertainty regarding these estimates. An ICC of 0.05 approximates to a moderate Cohen effect size (0.5) and this is close to the mean of the estimates from Barrowclough et al.^31^ The study is robust against larger values of the intracluster correlation for group treatment. For example, if the intracluster correlation coefficient is as large as 0.1, power will still be 86.7%. We therefore believe that the value of 0.05 is a reasonable choice of ICC to use for sample size calculation. In some smaller sites, to reduce the wait for participants for PHP groups to start smaller PHP groups with five to six (10–12 SCID-positive) participants may be run. Reducing the group size to an average of five participants and recruiting a larger number of groups would further increase the power to 91%.

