### Statistical analysis

We will use intention to treat analysis. Statistical analysis will be carried out with a logistic random effects model to estimate the odds ratio of recovery between treatment arms, with additional covariates of centre, baseline severity of depression and education (<8 years, ≥8 years). The analysis will be used for both the primary outcome measure (recovery at 4 months, end of intervention) and the further outcome (at 12 months). Random intercepts will be included for the therapy groups, with control participants treated as clusters of size 1, using the methods described by Roberts and Roberts^30^ for the analysis of a partially nested trial.

The treatment effect for quantitative secondary outcome measures will be estimated with a similar approach, with a linear random effects model and a random intercept for therapy group. Baseline value of the measure, centre, parity and educational level will be included as covariates. Statistical analyses will investigate baseline factors that predict non-response by using a logistic random effects model, as non-response may be clustered by therapy group. Sensitivity analysis will be carried out under a range of assumptions regarding missing data informed by the analysis of non-response.

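### The covariates fixed for quantitative secondary outcomes leave out infant age, which may cost some precision, but no bias, on the child-development outcome

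*Protocol article*

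**What the plan says.** The inclusion criteria admit women "living with their infant(s), who are aged up to 12 months". The child is therefore roughly 12 to 24 months old at the 12-month visit.

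Under Secondary outcome measures, child development is assessed by the Ages and stages questionnaires: "this series of 11 questionnaires each include 30 closed questions on five domains of child development", and "mothers will finish the questionnaire both at baseline and 12-month follow-up". Table 1 agrees, with no assessment at 4 months. No other listed outcome is measured on the child.

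Under Statistical analysis, quantitative secondary outcomes are analysed "with a linear random effects model and a random intercept for therapy group". The adjustment set is then named: "Baseline value of the measure, centre, parity and educational level will be included as covariates". No outcome has its own list.

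The article does not say which questionnaire in the series an infant receives, whether scores are standardised for age, or whether this outcome is analysed as a score or against a cut-off. It gives no standard deviation, target difference or age-score correlation for it.

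**The concern.** For a maternal scale such as the PHQ-9, the baseline value comes from the same instrument in the same adult, and the named list is a sensible general choice. Child development differs. The baseline may be taken from an infant of a few weeks or of nearly a year, and the follow-up from a child about 12 months older. Age is an obvious candidate predictor of the later score, and a baseline score that spans this age range may not carry all of that information. Whatever age still explains after the listed covariates stays in the residual and widens the confidence interval.

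The covariate list is a stated choice, and it includes parity, which the primary model does not. The point therefore concerns what the article fixes, not a gap left to the statistical analysis plan. The introduction cites harm to children's psychological and cognitive development as part of the case for treating postnatal depression, so precision on the one child outcome has some value.

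**Working it through.** **Inputs from the article (Sample size).** "We will recruit 720 participants and randomise 360 into each arm". The target is recovery of 55% with the intervention against 40% without it, and the stated power is 90%. The calculation is made "assuming an intraclass correlation (ICC) for group treatment of 0.05, a 75% follow-up and a 5% significance level". The mean analysed group size is 6.75. Analysed number per arm: 0.75 × 360 = 270. The test is taken as two-sided.

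**Step 1: reproduce the plan's own power (primary outcome).**
- Design effect, intervention arm only: 1 + (6.75 − 1) × 0.05 = 1.2875.
- Effective intervention n: 270 / 1.2875 = 209.7, against 270 controls.
- Pooled proportion: (209.7 × 0.55 + 270 × 0.40) / 479.7 = 0.4656. Null standard error: 0.0459. Alternative standard error: √(0.2475/209.7 + 0.24/270) = 0.0455.
- Power: Φ[(0.15 − 1.96 × 0.0459) / 0.0455] = 90.65%, against 90% stated.

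The article's other two figures also reproduce closely: 87.1% against 86.7% for an ICC of 0.1, and 91.7% against 91% for groups of five. None of them concerns the child outcome.

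**Step 2: precision on the child outcome.** Assumptions: 270 per arm at 12 months (the 75% is given for 4 months only), ICC 0.05 in the intervention arm, and a residual correlation r between infant age and the 12-month score after the listed covariates. The article does not give r, so 0 to 0.5 is used. The percentage change in the standard error (SE) does not depend on the 270.

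- SE without age, in residual SD units: √[(1.2875 + 1)/270] = 0.0920.
- SE with age: 0.0920 × √(1 − r²).
- Difference detectable with 80% power: 2.8016 × SE, where 2.8016 = 1.9600 + 0.8416.
- Equivalent gain in sample size: 1/(1 − r²) − 1.
- New power of a comparison that had 80%: Φ[2.8016/√(1 − r²) − 1.96].

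| r | SE | Cut in SE | Equivalent gain in n | Detectable difference (residual SD) | Power, from 80% |
|---|---|---|---|---|---|
| 0 | 0.0920 | 0% | 0% | 0.258 | 80.0% |
| 0.1 | 0.0916 | 0.5% | 1.0% | 0.257 | 80.4% |
| 0.2 | 0.0902 | 2.0% | 4.2% | 0.253 | 81.6% |
| 0.3 | 0.0878 | 4.6% | 9.9% | 0.246 | 83.6% |
| 0.4 | 0.0844 | 8.4% | 19.0% | 0.236 | 86.4% |
| 0.5 | 0.0797 | 13.4% | 33.3% | 0.223 | 89.9% |

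The table holds the ICC at 0.05 after adjustment. If the therapy-group variance is instead left unchanged by adjusting for age, the SE ratio is √[(2(1 − r²) + 0.2875)/2.2875], where 0.2875 = 5.75 × 0.05. The cuts are then slightly smaller: 1.8%, 4.0%, 7.3% and 11.6% at r = 0.2, 0.3, 0.4 and 0.5.

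**Step 3: check for bias by simulation.** There were 3,000 trials per scenario, with 270 per arm, infant age uniform over 0 to 12 months, ICC 0.05 in the intervention arm and a true effect of 0.20. The mean estimate was 0.200 to 0.202 with or without age in the model. The SE ratio (with age over without) was 1.00, 0.99, 0.97 and 0.92 for a direct age effect of 0.1, 0.2, 0.33 and 0.5 SD per SD of age. With no age effect it was 1.001, so an uninformative covariate cost almost nothing.

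**The case against.** The strongest case against is that this is a general covariate sentence in a condensed article. Scoring of a multi-form instrument, and any extra covariate for one unpowered secondary outcome, can be left to a statistical analysis plan that is not shown. A series of 11 questionnaires may well be assigned or scored by age. If so, much of the age effect is already gone, the baseline score removes more, and r could be close to zero. The outcome might also be analysed against a cut-off, in which case the linear model would not apply.

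Most of this stands, and it limits the point. A reader might infer that raw scores from different forms are pooled, but the article says only that the baseline value of the measure is used. A reader might also infer that precision is certainly wasted, but without an age-score correlation the loss cannot be shown, and the range must include zero. Nor does the 75% follow-up figure support a warning about age imbalance among women retained for this outcome, because it is given for 4 months. Chance imbalance at randomisation is in any case already reflected in the standard error. How the forms are put on a common scale is a detail that may be left to the analysis plan and is not a finding here.

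One thing survives: the article does name a covariate set for these outcomes, and infant age is not in it.

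**Conclusion.** The point holds as a minor, optional improvement. As written, the model for quantitative secondary outcomes omits infant age for the one outcome where it is an obvious candidate predictor. There is no bias and no threat to validity. The possible cost is precision: 0% to about 13% of the standard error for an assumed residual correlation of 0 to 0.5. It is about 2% or less up to r = 0.2, and reaches 8% or more only from about r = 0.4. If questionnaires or scoring are age-matched, expect the low end. These figures assume analysis as a quantitative score and an ICC of 0.05 in the intervention arm. The absolute standard errors and detectable differences also assume 270 women per arm at 12 months. The primary analysis, the sample size and the other secondary outcomes are not touched.

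**What to change.** Where the Ages and stages outcome is analysed as a quantitative score, add infant age at baseline to the covariates named under Statistical analysis, for this outcome only, and specify it before unblinding. Age at baseline is enough: it precedes randomisation and, apart from variation in visit timing, fixes age at the 12-month visit.

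The cost is one extra model term. Infant age has to be established to confirm eligibility, so no new data are needed. With about 540 women (2 × 270, or fewer if 12-month retention is lower), the loss if age proves uninformative is negligible.
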